
### Sample size estimation

Sample size for the quantitative phase was determined based on the primary outcome of this study (patient satisfaction). According to previous trials, a minimally important difference of 10 mm was considered for the estimation [40], as well as a standard deviation of the difference in satisfaction of 7.5 mm [41]. A two-sided alpha of 0.01 will be also considered to compensate for the number of secondary outcomes. Based on a power of 90%, this trial requires at least 21 participants [42]. An additional 20% will be added to the planned sample to compensate for possible dropouts, thus resulting in a total of 26 participants.

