**Methods/design:**

We will carry out a randomized cross-over clinical trial comparing Novaloc attachments to Locators for single-implant mandibular overdentures in edentate elderly individuals. Participants will be followed for three months with each attachment type; patient-based, clinical, and economic outcomes will be gathered. A sample of 26 participants is estimated to be required to detect clinically relevant differences in terms of the primary outcome (patient ratings of general satisfaction). Participants will choose which attachment they wish to keep, then be interviewed about their experiences and preferences with a single implant prosthesis and with the two attachments. Data from the quantitative and qualitative assessments will be integrated through a mixed-methods explanatory strategy. A last quantitative assessment will take place after 12 months with the preferred attachment; this latter assessment will enable measurement of the attachments’ long-term wear and maintenance requirements.

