### Randomization, allocation, and blinding

The sequence in which each participant will receive the two attachments will be decided by a list of random, computer-generated codes. Sequences will be decided based on the initial system used (ratio: 1:1): (1) A-B; (2) B-A. These codes will be secured in opaque sealed envelopes and one will be opened for each participant immediately before attachment insertion. A researcher not involved with the trial will prepare these codes and envelopes, following a simple randomization method stratified by ridge morphology (favorable - Cawood and Howell’s class III vs unfavorable/others). In spite of eventual imbalances in the number of participants per sequence, simple randomization can preclude prediction of allocation by researchers [26].

Although it will not be possible to blind participants and care providers to the treatments, researchers unaware of the participants’ allocations will conduct the outcomes assessment whenever applicable (blind assessor 1: patient-reported outcomes; blind assessor 2: cost data; refer to “Study Outcomes” below for details). We will also avoid mentioning to participants any expectation regarding performance of one system over the other. Appointments will be organized in such a way as to minimize communication between participants and to prevent potential contamination. We will request that participants keep their attachments confidential and not discuss them with the research member involved in the outcome assessment.

To confirm blinding effectiveness, participants will answer which attachment they think they have (experimental or traditional) at the end of the six-month follow-up and their conviction about the strength of their response from 0 to 10 (“not at all certain” and “extremely certain,” respectively) [27].

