### Statistical analysis

All quantitative data will be entered and analyzed in a blinded fashion. Such data will undergo descriptive analysis and will be transformed in cases of considerable deviation from normality. Clinical data will generate a composite variable representing clinical adversities; both the compound measure and separate event types will be analyzed.

Mixed linear models will be used to test the effect of interventions and follow-up time (three vs six months), as well their interaction.

The primary outcome will be further tested for carryover effects by fitting another mixed linear model with the two treatment periods and testing for the intervention by period interaction. Other approaches to assess the primary outcome will involve the inclusion of the randomization strata (ridge shape), age, baseline results, and perceived denture base rotation as covariates in separate models, one covariate each time. Analysis for carryover will be performed for cost estimates.

Results will be evaluated according to the intention-to-treat principle. In the case of unbalanced missing data among interventions or loss of 5% (*n* > 1) or more of participants, different strategies will be attempted for imputing primary outcome data, as recommended by Dziura et al. [43]; multiple imputation will be used for patient satisfaction based on least squares regression with at least five datasets. In the case of “missing not at random” (MNAR) data, we will repeat analyses after a baseline-observation-carried-forward approach (i.e. withdrawn participants will be considered as dissatisfied as before receiving implants). A second analysis will be performed with imputed values and cross-checked. Statistical tests will be performed using SPSS 21.0, considering α = 0.05.

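### The stated 21 participants does not follow from the stated inputs: an SD of the difference of 7.5 mm needs 12 or 13, and 21 fits 7.5 mm as a within-participant SD

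*Protocol article*

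**What the plan says.** The Sample size estimation section of the protocol article gives all the inputs of a paired calculation:

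- Effect: "a minimally important difference of 10 mm was considered for the estimation".
- Variability: "as well as a standard deviation of the difference in satisfaction of 7.5 mm".
- Type I error: "A two-sided alpha of 0.01 will be also considered to compensate for the number of secondary outcomes".
- Result: "Based on a power of 90%, this trial requires at least 21 participants".
- Dropout: "An additional 20% will be added to the planned sample to compensate for possible dropouts, thus resulting in a total of 26 participants".

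The section on randomization confirms a two-sequence cross-over: "Sequences will be decided based on the initial system used (ratio: 1:1): (1) A-B; (2) B-A". Each completer therefore contributes one within-person difference, and the SD of that difference is the quantity the calculation needs. The abstract repeats the final total: "A sample of 26 participants is estimated to be required to detect clinically relevant differences". The article gives no correlation, second variance or formula, only a reference for the calculation.

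**The concern.** The standardised effect implied by the text is 10/7.5 = 1.33 SDs of the difference. An effect that large needs very few pairs even at alpha 0.01, so 21 looks too many. A common slip would explain it: the SD of a single measurement within a participant and the SD of the difference between two such measurements differ by a factor of √2, and one is easily labelled as the other.

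This paragraph is the only justification given for the trial's size. If the result is null, readers will use the planned variability, power and detectable difference to judge what the trial was designed to exclude. If those figures cannot all be true, that judgement has no firm basis. A later trial that took 7.5 mm at face value as an SD of differences could also be planned much too small.

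**Working it through.** **Inputs** (all from Sample size estimation): difference δ = 10 mm; SD 7.5 mm, labelled as that of the difference; two-sided α = 0.01; power 90%; stated result n = 21.

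**Method.** For a paired comparison of n differences with SD s, the normal approximation is n = (z₀.₉₉₅ + z₀.₉₀)² × (s/δ)². The exact power comes from the noncentral t distribution with noncentrality δ√n/s. The degrees of freedom are n − 1 (simple paired t) or n − 2 (2×2 cross-over with a period effect).

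**Step 1: inputs as labelled, s = 7.5 mm.**

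- Normal approximation: (2.576 + 1.282)² × (7.5/10)² = 14.88 × 0.5625 = 8.37, so 9.
- Exact t, df n − 1: n = 12, power 90.7%.
- Exact t, df n − 2: n = 12 gives 89.4%, just short; n = 13 gives 93.0%.

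The stated inputs therefore give 12 or 13. Twenty-one is larger by 8 or 9 participants (21/13 = 1.62; 21/12 = 1.75).

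**Step 2: reproducing 21.** Let 7.5 mm be the within-participant SD of one measurement. Then s = 7.5 × √2 = 10.61 mm.

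| n | Power, df n − 1 | Power, df n − 2 |
|---|---|---|
| 20 | 89.7% | 89.3% |
| 21 | 91.6% | 91.3% |

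Twenty-one is the smallest n that reaches 90% under either choice of df. Working backwards with δ, α and power fixed, the largest SD of the difference for which 21 gives 90% power is 10.8 to 10.9 mm.

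**Step 3: other explanations, keeping 7.5 mm as the SD of the difference.**

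| Variant | n |
|---|---|
| Even n for balanced sequences (df n − 2) | 14 |
| Inflation for a Wilcoxon test | at most 16 |
| Power raised to 95% | 14 |
| Power raised to 99% | 18 |
| α = 0.05, the level in Statistical analysis | 9 |

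None reaches 21. A two-independent-group t calculation with SD 7.5 mm gives 19 per group. That is also not 21, does not fit the design, and again treats 7.5 mm as the SD of a single measurement.

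**Step 4: what each reading implies at the planned size** (two-sided α = 0.01).

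| SD of the difference | Power for 10 mm, n = 21 | Power for 10 mm, n = 26 | Detectable at 90% power, n = 21 |
|---|---|---|---|
| 7.5 mm | 99.9% | over 99.9% | 6.9 mm |
| 10.6 mm | 91% | 97% | 9.8 mm |

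With 26 completers and an SD of the difference of 7.5 mm, the detectable difference is 6.1 mm.

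**Step 5: the total.** 21 × 1.2 = 25.2, rounded up to 26. The total follows from 21 and inherits the problem; it is not separate evidence of it.

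**Step 6: consequence of reusing the figure.** If the true SD of the difference is 10.6 mm, a trial planned on 12 or 13 participants would have only 56% to 64% power.

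**The case against.** The strongest reply is that nothing operational is at stake. The text calls 21 a minimum, and under both readings 21 completers reach the stated 90% power for 10 mm at alpha 0.01. If 7.5 mm is correctly labelled, the trial is conservatively sized; if not, 21 is right and only a label is wrong. A null result will in any case be judged mainly on its confidence interval, which uses the variance observed in the trial. The sources for the SD and for the calculation are not available here, so the within-participant reading is an inference, however well it fits.

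Most of this stands. The trial is not underpowered on either reading, and there is no case for changing enrolment. The within-participant explanation should be put as the reading that reproduces the figure, not as established fact. Other routes to 21 exist: 95% power by the normal approximation at alpha 0.01, or 95% power at alpha 0.02 by exact t. They also need the within-participant SD, and they depart from the stated power or alpha.

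What the reply does not do is remove the contradiction. The section says that 21 are required for 90% power with a 7.5 mm SD of the difference, and that statement is false. Nor is this a detail left to a fuller document, because the inputs and the result are both printed and disagree.

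**Conclusion.** The point holds. With the inputs as written, the required number is 12 or 13, not 21, and the power at 21 is about 99.9%, not 90%. The stated 21 is matched exactly if 7.5 mm is the within-participant SD, which makes the SD of the difference 10.6 mm. The two readings differ by a factor of 2 in variance, by 8 or 9 participants, and between 6.9 mm and 9.8 mm in the difference detectable with 21 completers.

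This rests on a paired or cross-over t test of the mean difference at the alpha and power given in the sample size section. The document alone cannot settle which reading is right. The error lies in the stated assumptions and power, and it must be corrected because the stated SD, sample size and power cannot all be true.

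**What to change.** Check in the cited source what the 7.5 mm describes, then make one of two changes to the sample size paragraph.

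- If it is the within-participant SD, say so and give the derived value: within-participant SD 7.5 mm, SD of the difference 10.6 mm. The 21 then follows.
- If it is the SD of the difference, keep the enrolment target but stop describing 21 as the number required for 90% power. State instead that 21 completers give about 99.9% power for 10 mm, or that they can detect 6.9 mm with 90% power, at two-sided alpha 0.01. The abstract's statement that 26 are required would need matching wording.

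In either case, add the test and degrees of freedom used, so that the figure can be reproduced. The cost is one source check and a wording correction; enrolment, design and analysis do not change.

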### Statistical analysis

All quantitative data will be entered and analyzed in a blinded fashion. Such data will undergo descriptive analysis and will be transformed in cases of considerable deviation from normality. Clinical data will generate a composite variable representing clinical adversities; both the compound measure and separate event types will be analyzed.

Mixed linear models will be used to test the effect of interventions and follow-up time (three vs six months), as well their interaction.

The primary outcome will be further tested for carryover effects by fitting another mixed linear model with the two treatment periods and testing for the intervention by period interaction. Other approaches to assess the primary outcome will involve the inclusion of the randomization strata (ridge shape), age, baseline results, and perceived denture base rotation as covariates in separate models, one covariate each time. Analysis for carryover will be performed for cost estimates.

Results will be evaluated according to the intention-to-treat principle. In the case of unbalanced missing data among interventions or loss of 5% (*n* > 1) or more of participants, different strategies will be attempted for imputing primary outcome data, as recommended by Dziura et al. [43]; multiple imputation will be used for patient satisfaction based on least squares regression with at least five datasets. In the case of “missing not at random” (MNAR) data, we will repeat analyses after a baseline-observation-carried-forward approach (i.e. withdrawn participants will be considered as dissatisfied as before receiving implants). A second analysis will be performed with imputed values and cross-checked. Statistical tests will be performed using SPSS 21.0, considering α = 0.05.

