In this mixed-methods randomized cross-over trial (RCT), we aim to produce evidence of the efficacy of using the Novaloc attachment system to retain single-implant mandibular overdentures, compared to a traditional cylindrical attachment (Locator), for edentate elder patients. The primary outcome of this study is ratings of general satisfaction on visual analog scale (VAS) measures following three months of use with each attachment type. Through qualitative interviews, we will also describe what characteristics of these systems are considered important to patients when stating their satisfaction and preferences; we will use this rich descriptive data to help explain the quantitative RCT results.

Secondary outcomes include: (1) specific domains of satisfaction (e.g. retention/stability and hygiene); (2) oral health-related quality of life (OHIP-EDENT); (3) economic variables; (4) perceived rotation of the mandibular overdenture; (5) clinician-based outcomes, i.e. success rate of implants/overdentures and clinical complications/maintenance needs; and (6) choice of attachment.

Participants will keep their chosen attachments for another 12-month period and we will evaluate the same outcomes.

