### Study hypothesis

The primary null hypothesis of the trial is that there is no difference in ratings of patient satisfaction for Novaloc and Locator attachments.

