### Study outcomes

All patient-reported outcomes, except for prosthesis rotation, will be collected at baseline, together with sociodemographic data, including age, gender, level of education, and income. Clinical data will be also collected before treatment, such as ridge morphology [28], amount of time edentulous, and age of existing dentures.

Participants will return for outcome assessment after three months using each attachment, for a total follow-up time of six months. A three-month period is enough to observe a significant decrease in the retention force of Locators [29] but is of unlikely length for adverse events associated with other components. Moreover, a slightly longer period, i.e. six months, results in similar patient satisfaction with mandibular overdentures [30]. Participants will be evaluated again 12 months following the cross-over trial for an appraisal of maintenance needs/adverse events. A 12-month period will be enough to reveal attachment maintenance events for most participants with Locators [21], as well as some uncommon events, e.g. denture base fractures [13].

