In each assessment session, participants will provide data on:Satisfaction with overdentures. The McGill VAS Satisfaction questionnaire [31] will be used to measure general satisfaction (primary outcome), as well as satisfaction with other functional aspects of the prostheses using 100 mm VAS. Other aspects include ability to chew, comfort, stability, aesthetics, ability to speak, and ability to clean. Some of the 13 items in the questionnaire include ability to chew specific foods (lettuce, soft bread, hard cheese, steak, raw apple, and raw carrot). These were selected because they represented different textures and hardnesses and were ranked by a group of complete denture patients from “very easy” to “very difficult” to chew. Patients will rate their ability to chew these foods on a 100 mm VAS with anchors of “not at all difficult to chew” to “impossible to chew.” Patients will be trained to use this type of scale before answering the questionnaires. Previous studies have shown good properties for the McGill VAS Satisfaction questionnaire. Besides good internal consistency and reproducibility [32], its ability to discriminate between different clinical conditions denotes good construct validity [30, 33].Oral health-related quality of life. Participants will be asked to complete the Oral Health Impact Profile for edentulous people (OHIP-EDENT), which is an abbreviated version of the original 49-item OHIP that was tested specifically with edentulous populations [34]. This questionnaire is composed of 20 items that can be grouped into subscales, representing different domains/dimensions of perceived impact, such as functional limitation or social disability. This abbreviated version shows good reliability and discriminant validity, similar to the original OHIP [34]. Although seven subscales were originally purported [35], we will use a four-domain model as recommended by recent factor analysis studies [36, 37].Overdenture rotation. Patient perception of rotation of the mandibular overdenture will be assessed by two questions, as used by Kimoto et al. [38]: (1) Does your denture lift at the back when you chew? (yes-no); (2) How much does the lifting of your denture bother you? (100 mm VAS).Clinician-based outcomes will be assessed for each three-month period. Participants will be evaluated based on a standardized clinical form, which will be completed immediately following each appointment. Overdentures will be classified as successful if they can function in the way that they were intended, with additional retention provided by the attachment system. For the determination of implant success and survival, the implants will be classified at each data collection appointment according to Misch et al. [39]. Clinical evaluation will also include the following parameters [30]: (a) presence of plaque; (b) presence of calculus; (c) depth of peri-implant pockets; (d) bleeding on probing; (e) signs of swelling or inflammation. The presence of suppuration and tenderness will also be noted. Probing depth will be measured at four sites for each implant (mesially, labially, distally, and lingually) using a periodontal probe.Treatment costs. We intend to gather data on both direct and indirect costs to compare the differences in cost-effectiveness between the two attachments systems. The effectiveness is measured by any difference in overall patient satisfaction (primary outcome) at baseline and at the three- and six-month follow-up visits. The size of the effect may vary at each of the two intervals. This analysis is based on the following assumptions: (1) the total cost at the end of the 6-month evaluation period would be the same between sequences 1 and 2; (2) the implant placements are deemed clinically successful at given intervals (three and six months post treatment); (3) no surgical or prosthetic complications are encountered during the six-month post-treatment period. Cost-effectiveness between the two attachments systems will be determined by calculating incremental cost-effectiveness ratios (ICER), based on baseline–post-intervention differences in satisfaction.

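### Perceived denture rotation, a secondary outcome measured only after randomization, is listed as an adjustment covariate in a supplementary model of the primary outcome; that model does not estimate the attachment effect named in the hypothesis

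*Protocol article*

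**What the plan says.** The hypothesis concerns the attachments as such: "The primary null hypothesis of the trial is that there is no difference in ratings of patient satisfaction for Novaloc and Locator attachments" (Study hypothesis).

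The main analysis in the Statistical analysis section is: "Mixed linear models will be used to test the effect of interventions and follow-up time (three vs six months), as well their interaction". It contains no rotation term.

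The same section then adds supplementary models. The sentence begins "Other approaches to assess the primary outcome will involve the inclusion of the randomization strata (ridge shape" and, after the closing bracket, continues with "age, baseline results, and perceived denture base rotation as covariates in separate models, one covariate each time". It does not separate rotation from the other three covariates, and it does not call the rotation model exploratory or a mediation analysis.

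Elsewhere the article describes rotation as follows:

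- The Background lists it among the secondary outcomes: "4) perceived rotation of the mandibular overdenture".
- Study outcomes states: "All patient-reported outcomes, except for prosthesis rotation, will be collected at baseline".
- Study outcomes fixes the timing of assessments: "Participants will return for outcome assessment after three months using each attachment, for a total follow-up time of six months".
- It is measured by a yes/no question on lifting during chewing and by a bother rating: "2) How much does the lifting of your denture bother you? (100 mm VAS".

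**The concern.** One variable is given two roles that do not fit together: a result of the attachment, and a quantity to hold constant when judging the attachment. Covariate adjustment leaves the meaning of a treatment comparison intact when the covariate is fixed before treatment. Ridge shape, age and baseline results meet that condition. Rotation cannot, because every value is obtained after a period of wearing one of the two attachments.

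Two things follow. If the attachment changes rotation and rotation changes satisfaction, the adjusted coefficient leaves out the part of the effect that runs through rotation. Separately, the bother item is a participant's complaint about the same denture, rated on the same kind of scale and at the same session as satisfaction. A shared rating tendency, or any other unmeasured common cause, would bias the adjusted coefficient even as an estimate of a direct effect.

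What is at stake is interpretation. The result would stand beside three legitimately adjusted models, introduced as another approach to the primary outcome, with nothing to tell the reader that it answers a different question.

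**Working it through.** **Step 1. Compare the four covariates.**

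| Covariate | Fixed before treatment? | Can it differ between a participant's two periods? |
|---|---|---|
| Ridge shape (stratum) | Yes | No |
| Age | Yes | No |
| Baseline results | Yes | No |
| Perceived rotation | No; no baseline value | Yes |

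Entered as main effects with complete data, the first three leave the within-participant contrast between attachments unchanged. Rotation, entered as its period-specific value, acts on that contrast directly.

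**Step 2. What the adjusted model estimates.** For each participant let D be the satisfaction difference (Novaloc minus Locator) and R the reduction in the rotation score under Novaloc. With fitted slope s of D on R,

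adjusted effect = total effect − s × mean(R).

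The two effects agree only if s = 0 or mean(R) = 0. The slope s absorbs both a causal path and any shared causes of the two ratings. Depending on the signs of s and mean(R), the adjusted effect can fall below or above the total effect.

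**Step 3. Inputs for an illustration.** The plan gives no figure for rotation, so there is none to reproduce on this point.

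- From Sample size estimation: difference 10 mm, two-sided alpha 0.01, 21 participants before dropout.
- SD of the difference: 7.5 × √2 = 10.6 mm, which treats the plan's 7.5 mm as a within-participant SD. This choice reproduces the plan's 21 (power 0.91 by the noncentral t). It serves only to calibrate the illustration.
- Assumed: mean(R) = 10 mm, SD of R = 10 mm, no shared causes, and a share m of the 10 mm effect running through rotation. The slope is then b = m × 10 / 10 = m.

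**Step 4. Results** (4,000 simulated trials of 21 participants per row, sequence included in the model):

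| Share m | 10 − b × 10 (mm) | Simulated adjusted (mm) | Simulated unadjusted (mm) | Power, unadjusted | Power, adjusted |
|---|---|---|---|---|---|
| 0% | 10.0 | 9.96 | 9.97 | 0.91 | 0.54 |
| 25% | 7.5 | 7.45 | 9.97 | 0.91 | 0.31 |
| 50% | 5.0 | 4.94 | 10.00 | 0.91 | 0.15 |
| 75% | 2.5 | 2.52 | 10.01 | 0.91 | 0.05 |

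The simulated estimates return the assumed shares, as the algebra says they must. They confirm the mechanism and say nothing about the true share.

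The power loss in the 0% row arises because the adjusted effect is read at R = 0, one SD from the mean of R. The variance is multiplied by about 1 + (10/10)² = 2, so the standard error rises from 10.6/√21 = 2.3 mm to about 2.3 × √2 = 3.3 mm. That loss also depends on the assumed rotation difference.

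**The case against.** The strongest reply is that the primary test is not touched. The null hypothesis is tested in a mixed model of intervention, follow-up time and their interaction. Rotation enters only afterwards, in its own model, so it cannot affect the main test or the models with ridge shape, age or baseline results. This stands in full. A reader might infer from the covariate list that the trial's main result will be adjusted for rotation; the text does not support that.

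Second, mediation is not shown. No part of the article states that Novaloc changes rotation relative to Locator; naming rotation as an outcome means only that a difference will be looked for. This also stands, which is why rotation is called a potential mediator here. It does not remove the point: a variable measured after randomization under each attachment is not a neutral adjustment covariate, whether or not mediation turns out to be present.

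Third, a reader might infer that half or more of a real effect would be adjusted away, or that the effect would seem to disappear. Such figures only return what is assumed. The range has to start at no loss, and nothing in the article says that a supplementary model overrides the main one.

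Fourth, asking whether rotation explains satisfaction is a reasonable question in a trial with an explanatory aim. That is so, but the explanatory strategy described is the use of qualitative findings to explain quantitative results. The rotation model is instead introduced as a further way of assessing the primary outcome, and that label is the defect.

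**Conclusion.** The point holds for one supplementary model. As written, the rotation-adjusted model conditions on a post-randomization secondary outcome and so does not in general estimate the total attachment effect in the null hypothesis. It may be biased in either direction if rotation ratings and satisfaction share unmeasured causes.

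The size cannot be determined from the documents. For an assumed 10 mm effect with 0 to 75% running through rotation, the adjusted estimate ranges from about 10 mm down to about 2.5 mm. This rests on rotation entering as a period-specific score, on the assumed 10 mm mean rotation difference, and on no shared causes; with shared causes, even the 0% case could move.

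Because the main analysis is intact, this is a should-fix matter, not a threat to the trial's primary conclusion.

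**What to change.** In the Statistical analysis section, do one of the following:

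1. Delete perceived denture base rotation from the covariate list and analyse it only as the secondary outcome it is; or
2. Keep the model but move it out of the list, call it an exploratory mediation analysis, state its assumption of no unmeasured common causes of rotation and satisfaction, and say that it is not an adjusted estimate of the primary effect.

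The models with ridge shape, age and baseline results are not open to this objection. The Long-term follow-up section adopts the same statistical strategies, so the corrected wording carries over to the 12-month data.

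The cost is a sentence of protocol or analysis-plan text. Visits, data collection and sample size do not change.
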